### Study recruitment and informed consent

This protocol was approved by the St. Jude Institutional Review Board and will be reviewed by LMIC local participating sites’ ethics committees. Recruitment will occur after the completion of the baseline BHAP administrative application and the hospital assessment questionnaire for the drug donation program. Participation in the BHAP program does not necessitate participation in this implementation research study, and AMGEN will not be involved in recruiting participants for the implementation study. If sites agree to participate, the baseline information collected for the BHAP program enrollment will be included in the study.

At LMIC sites, all pediatric oncology staff who participate in the training program will complete a brief knowledge assessment survey. However, the remainder of the implementation evaluation will occur through a site-specific implementation team. This team will be identified by the site PI and consists of multidisciplinary members who have demonstrated organizational leadership in the implementation of blinatumomab and will contain at least two physicians, two nurses, and one pharmacist. This group selection will satisfy pragmatic constraints due to limited resources and time in LMIC settings but will also provide rich representation within and between different provider roles within an institution and thematic saturation across multidisciplinary experts. These providers will give consent to complete additional surveys and participate in semi-structured interviews.

Secondary data related to implementation costs and routine clinical care will be collected. Deidentified patient information will be required to confirm patient suitability for participation in the BHAP program and for routine monitoring during medication administration and clinical care.

### Aim 1: To conduct a formal assessment to characterize determinants that influence blinatumomab implementation in LMICs

For aim 1, this study will use mixed methods to evaluate the hypothesis that barriers related to inner setting and intervention characteristics impact the implementation of blinatumomab in LMICs. This will include the assessment of (1) capacity, (2) key barriers (readiness, climate, intervention complexity, cost), and (3) perceptions of leading indicator implementation outcomes (feasibility, acceptability, and appropriateness) from multiple stakeholders. For the three pilot sites, implementation assessments will occur 1 year after the training; however, for future sites, these will be part of the upfront baseline assessment. Assessments will be repeated at 3, 6, and 12 months post-training to characterize changes in perceived barriers and implementation outcomes over time (Table 4).

**Table 4 Tab4:** Assessment administration time points, target respondents, and frequency. Measurement tools including the type of data, key respondents, frequency, and time points of administration

Survey topic	Method	Respondent(s)	Frequency	Time point(s)
**Hospital assessment questionnaire**	QUAN	LMIC site physician champion	1 time	Prior to BHAP enrollment
**Complexity assessment**	QUAN	Implementation team	4 times	Pre-training, 3 and 6 months, and 1-year post-training
**Implementation Climate Scale (ICS)**	QUAN			
**Organization Readiness for Implementing Change (ORIC)**	QUAN			
**Acceptability of intervention (AIM)**	QUAN			
**Intervention Appropriateness Measures (IAM)**	QUAN			
**Feasibility of Intervention (FIM)**	QUAN			
**Knowledge assessment: nurses**	QUAN	All nurses	4 times	Pre-training, 3 and 6 months, and 1 year post-training
**Knowledge assessment: pharmacy**	QUAN	All pharmacists		
**Knowledge assessment: physician**	QUAN	All physicians		
**Training material feedback survey**	QUAL	Implementation team	1 time	3 months post-training (after the 1st patient received blinatumomab)
**Semi-structured group interviews:** **1) Training program feedback and site-specific barriers** **2) Site-specific fidelity vs adaptation**	QUAL	Implementation team	2 times	3 months post-training (after the 1st patient received blinatumomab) and 12 months post-training
**Implementation strategy feedback**	QUAN	Key stakeholders (implementation team, industry, St. Jude)	1 time	Annual review
**Program evaluation group interview**	QUAL			
			1 time	Annual review

*LMICs* Low- and middle-income countries, *BHAP* Blincyto® Humanitarian Access Program, *QUAN* Quantitative, *QUAL* Qualitative

We selected well-established measurement tools that have been validated in HICs and were chosen because they are pragmatic, reviewed and agreed upon by stakeholders, and when compiled have less than 50 questions that can be completed in less than 30 min. The quantitative surveys to assess barriers include the Implementation Climate Scale (ICS) [24], Organizational Readiness for Implementing Change (ORIC) [25], and a complexity assessment. Implementation outcome survey assessments include Acceptability of Intervention Measure (AIM), Intervention Appropriateness Measure (IAM), and Feasibility of Intervention Measure (FIM) [26]. These measures of implementation outcomes were selected for their salience with stakeholders and because they are considered “leading indicators” of implementation success for early-stage initiatives [26]. Survey data collected online through Qualtrics will be housed at the Department of Global Pediatric Medicine at St. Jude.

The research team will conduct two semi-structured group interviews with the implementation team to collect additional insights into the site-specific determinants. Interview #1 will be done 3 months after training and after the site has started administering blinatumomab. The CFIR Interview Development Tool will guide the development of the interview guide and will be adapted based on experience with the pilot sites [27]. The team will ask open-ended questions about the implementation processes, barriers, and facilitators and will elicit feedback on the training program. Interview #2 will be done 1 year after training, wherein the research team will ask open-ended questions on site-specific fidelity vs adaptations to recommended administration guidelines, strategies, emerging determinants, costs, team dynamics, adequacy of training program, utility of standardized documentation tools, and parent perception of treatment.

Interviews will be audio-recorded and transcribed verbatim, and the team will use thematic coding methods to analyze and interpret the results. Written transcripts will be reviewed independently by two research team members to identify emergent themes to build a codebook. Then, each transcript will be reviewed again using the codebook. The thematic coding process will focus on process improvement.

Descriptive statistics will be used to characterize the barriers and facilitators to blinatumomab implementation in LMICs. This will include describing core components of implementation, such as site infrastructure, climate, readiness, and intervention complexity. The survey will be summarized by frequency tables and cross-tabulation to study any associations. The chi-squared and Fisher’s exact test will be used to assess the associations. Comparisons will be made with assessments of barriers done over time (pre-training; 3, 6, and 12 months post-training). Univariate and multivariable logistic regression analysis will be used, as appropriate, to study the correlations among scores of clinical infrastructure, readiness, climate, and intervention complexity with implementation outcomes (feasibility, acceptability, and appropriateness) within and across institutions. Collectively, this information will be used to understand barriers and site-specific adaptations to modify the strategy approach and training program for medication delivery.

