### Collaborators and setting

This study is being conducted in collaboration with BHAP. LMIC sites where blinatumomab is not commercially available were identified and stratified into two groups: group 1, characterized by established pediatric cancer units, experienced bone marrow transplant centers, and specialized chemotherapy pharmacists; group 2, characterized as developing pediatric cancer and bone marrow transplant programs (autologous only or none) and overlapping nursing and pharmacist responsibilities.

The experience in the three group 1 pilot sites will inform the characterization of the future grouping in the model to facilitate expansion into future sites.

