### Study participants

The training program will be administered to all multidisciplinary pediatric oncology staff at each site. Evaluation data will be collected from multiple stakeholders: LMIC pediatric oncology staff, pilot site implementation team, pharmaceutical industry representatives, and multidisciplinary academic providers at St. Jude. The study will also collect secondary data from ~ 50 children enrolled in the BHAP program who received blinatumomab. Table 3 describes the inclusion criteria.

**Table 3 Tab3:** Inclusion criteria for primary and secondary data collection

**Primary data study participant group**	**Primary data inclusion criteria**
Local site physician champion	Submit an application for BHAP program enrollment
Multidisciplinary local site pediatric oncology staff	Attend both 90-min synchronous training sessions or watch session recording online
Local site implementation team	Will include a minimum of 2 physicians, 2 nurses, and 1 pharmacist at each LMIC site, who attended both training sessions and participated in frontline management of patients receiving blinatumomab in the inpatient setting
Key stakeholders	Representatives from the pharmaceutical company actively involved in the drug donation program Representatives from St. Jude actively involved in the BHAP program LMIC site implementation team
**Secondary data study participant group**	**Secondary data inclusion criteria**
Patients	Satisfy BHAP program enrollment criteria to receive blinatumomab, parental consent to receive blinatumomab (obtained by a local physician), and initiate blinatumomab infusion

*LMIC* Low- and middle-income countries, *BHAP* Blincyto® Humanitarian Access Program

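### Aim 1's association tests either ignore the order of the survey scores or, read as binary logistic regression, cut the outcome in two; at the minimum pilot sample of 15 this costs power that rank or ordinal methods would keep

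*Protocol article*

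**What the plan says.** The statistical paragraph of the Protocol article's Aim 1 section names two layers of analysis.

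- **Tables.** "The survey will be summarized by frequency tables and cross-tabulation to study any associations". Then: "The chi-squared and Fisher’s exact test will be used to assess the associations".
- **Regression.** "Univariate and multivariable logistic regression analysis will be used, as appropriate, to study the correlations among scores of clinical infrastructure, readiness, climate, and intervention complexity". The outcomes in these models are the three implementation outcome measures, and the relation is to be examined both inside each site and between sites.

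The article names no rank, trend or ordinal method. The barrier measures are the Implementation Climate Scale, the readiness scale and a complexity assessment; the outcome measures are the acceptability, appropriateness and feasibility instruments. Research question 3 asks whether readiness, capacity and perceived complexity correlate with successful implementation.

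On numbers, Table 3 says of the local implementation team: "Will include a minimum of 2 physicians, 2 nurses, and 1 pharmacist at each LMIC site". Collaborators and setting refers to three group 1 pilot sites. No sample size, significance level or power is given for the survey analyses.

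**The concern.** The research question is about ordered quantities: does a higher readiness score go with a higher feasibility score? Chi-squared and Fisher's exact tests treat categories as unordered and do not show which way a relation runs. A multi-item score must also be grouped before it can be tabulated, or the table is nearly empty. Fifteen people spread over a 3 x 3 table average 15/9 = 1.7 per cell.

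Logistic regression is better placed, because the determinant score can stay uncut and the odds ratio has a sign. In its usual binary form, however, it needs a two-level outcome, so the acceptability, appropriateness and feasibility scores would be split and the information within each half discarded.

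The Aim 1 results are to be used to adapt the strategy and the training, and Aim 3 compiles them into the Implementation Roadmap. A real determinant could look unrelated to the outcome only because the test was insensitive.

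**Working it through.** **Inputs from the article.** At least 2 + 2 + 1 = 5 team members per site (Table 3) at three pilot sites, so n is at least 3 x 5 = 15. The tests are those named in the Aim 1 paragraph. The article gives no power figure to reproduce.

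**Inputs assumed.** Two-sided 5% level; one wave; one row per person; independent respondents; two latent normal traits with correlation rho. Two score models were used:

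- Model A: each score is the mean of four five-level items, each with loading 0.8.
- Model B: each score lies on a 1-5 scale in steps of 0.25, with mean 4 and SD 0.6.

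**A check by hand.** Suppose a median split puts 8 high and 7 low on both scores. The chance of k people being high on both is C(8,k) x C(7,8-k) / C(15,8), with C(15,8) = 6435.

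- k = 7 (13 of 15 people concordant): two-sided p = (56 + 1 + 8)/6435 = 0.010.
- k = 6 (11 of 15 concordant): two-sided p = (588 + 56 + 1 + 196 + 8)/6435 = 849/6435 = 0.13.

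With these margins nothing lies between the two. Fisher's test finds a positive relation only if at most 2 of 15 people fall on the wrong side.

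**Simulated power, n = 15, rho = 0.6 (range over score models)**

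| Method | Power | Spearman minus method |
|---|---|---|
| Spearman, uncut scores | 47-62% | - |
| Fisher, median split | 20-25% | 27 to 37 points |
| Logistic, likelihood-ratio test, outcome split | 42-54% | 5 to 8 points |
| Logistic, Wald test, outcome split | 8-10% | 39 to 52 points |

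The likelihood-ratio test rejects about 7.5% of the time under no association, so its power is somewhat flattered. Spearman rejects about 5%. Repeat runs put the likelihood-ratio test at 39-52% and the Wald test at 7-9%, so differences of a few points should not be over-read.

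**Other correlations, n = 15, Model B**

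| rho | Spearman | Fisher | Chi-squared 2x2 | Chi-squared 3x3 | Logistic, likelihood ratio |
|---|---|---|---|---|---|
| 0.5 | 45% | 16% | 21% | 16% | 37% |
| 0.6 | 62% | 23% | 31% | 23% | 50% |
| 0.7 | 80% | 35% | 44% | 36% | 67% |
| 0.8 | 94% | 50% | 61% | 53% | 85% |

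**Larger samples, rho = 0.6.** At n = 30, Spearman against Fisher is 79% against 31% under Model A and 92% against 46% under Model B; likelihood-ratio logistic regression under Model B is 82%. At n = 45 (Model B) the figures are Spearman 99%, Fisher 73% and logistic 93%.

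**Infrastructure score.** One physician per site completes the hospital questionnaire (Phase 2, Table 4), so this score takes at most three values and is constant within a site. Permuting respondents within a site leaves any association statistic with it unchanged, so such a test always gives p = 1.

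**The case against.** A reader might infer that the plan looks for determinants only through unordered tables, that direction cannot be recovered, and that most of the power is lost. The article does not support this. Logistic regression is the method it names for determinant scores against implementation outcomes; that method can keep the predictor uncut, gives a signed estimate and, with a likelihood-ratio test, comes within about 5 to 8 points of Spearman in the main comparison. Even among the table tests, an uncorrected 2x2 chi-squared loses about half of Spearman's power or less at correlations of 0.6 and above.

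Other points also stand:

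- The table sentences do not say that scores will be cut. Site, role and single items are categorical, and Fisher's exact test suits nominal items.
- Fifteen is a minimum, not a fixed size, and later sites will add respondents.
- No significance rule governs entry to the Roadmap. Research question 3 also draws on interviews, and version 1.0 goes to a focus group and stakeholder survey. That a non-significant table would remove a barrier is a risk, not a stated rule.
- An outcome cut-point is detail that a journal article may leave to a fuller document, so its absence is no fault.

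What remains is the choice of methods that the article does state. The chi-squared and Fisher sentence is general, the regression is to be used as appropriate, and nothing named keeps both scores ordered unless the logistic model is meant to be ordinal.

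**Conclusion.** The point holds in a limited form. The Aim 1 paragraph names unordered tests and a logistic regression which, read as binary, splits the outcome; neither uses both ordered scores in full. At 15 respondents and a latent correlation of 0.6, the loss against Spearman is about 27 to 37 points for Fisher after a median split, 39 to 52 for the Wald logistic test and 5 to 8 for the likelihood-ratio logistic test. The loss to Fisher remains large at n = 30.

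The sizes depend on assumed score models, cuts and correlations, and on independent respondents. Clustering within three sites and repeated answers would affect every method compared. Even the best method here has only about 47-62% power at n = 15, so a null result should not be read as absence of a relation. This is a worthwhile, nearly free improvement and does not invalidate the study.

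**What to change.** In the Aim 1 statistical paragraph:

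1. Keep frequency tables and cross-tabulations for description, and Fisher's exact test for pairs of truly nominal items.
2. For each pair of scores, report a Spearman or Kendall correlation on the uncut scores, separately at each wave, with a 95% interval.
3. Where a regression is wanted, model the uncut outcome score by an ordinal (proportional-odds) or linear model in place of a dichotomised outcome.
4. If permutation p-values are used, permute within site only for respondent-level scores (readiness, climate, complexity). Report the infrastructure score descriptively, since it is constant within each of three sites.

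The cost is analysis wording only, with no new data or respondents. The one small downside is that a rank correlation can miss a non-monotone relation, which the retained tables would show.

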### Phase 3: Training program design and delivery

In order to prioritize patient safety and to build knowledge base and skills for the medical team to recognize and respond to AEs, we selected a training program as our primary strategy. The BHAP core team created learning objectives informed by LMIC preliminary capacity assessments and site-specific multidisciplinary training needs to tailor the program to the supportive care capacity of sites. These objectives guided the content creation for a comprehensive, context-adapted training program, including didactic presentations, treatment templates, administration and management guidelines, role-specific workflow materials, and caregiver handouts. Materials were developed by the St. Jude multidisciplinary team, and the content was reviewed by the BHAP core team. Given the COVID-19 pandemic restrictions, we transitioned to an online program, with virtual synchronous sessions and recordings posted to an online classroom on the Cure4Kids platform (http://www.cure4kids.org) along with workflow materials. For pilot sites, all training materials and surveys were administered in English; however, translation and validation will be performed based on the needs of future sites. Training was delivered to 78 healthcare providers (25 physicians, 36 nurses, and 17 pharmacists) and sessions conducted independently for each pilot site as two 90-min live, interactive virtual sessions. The content for the first session focused on general information related to blinatumomab indications, mechanism of action, efficacy, and AE profile and was delivered to the combined multidisciplinary team. The second session were provider-specific, with content focused on the management issues related to roles. These didactic sessions were facilitated by a St. Jude pediatric oncologist, a nurse, and a pharmacist, with time for group discussion. The training meetings highlighted the importance of prompt response when managing patients on immunotherapy and modeled risk-reducing communication techniques between providers. After the multidisciplinary team attended the two training sessions, centers could apply for blinatumomab on a per-patient basis, at which point the medication would be shipped and sites could begin administration.

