### Training program evaluation

The resource-adapted training program will be evaluated in three ways. First, a knowledge assessment survey will be administered to all pediatric oncology providers who participated in the BHAP training program at LMIC sites. For pilot sites, this will be administered as part of a nested post-training assessment. Future sites will receive a baseline survey prior to training and will be repeated at 3, 6, and 12 months post-training to determine the role-specific knowledge related to the preparation, administration, and management of patients receiving blinatumomab. Second, the implementation team will complete an online Training Material Feedback Survey, designed by St. Jude, and participate in semi-structured interview #1 with the site-specific implementation team. The team will ask open-ended questions on the utility of the training program and workflow tools, experience with real-world administration, and additional training needs. Third, a standardized documentation tool was designed a priori by the multidisciplinary providers at St. Jude to record infusion interruptions and will be tested in pilot sites and adapted based on this cohort. It will be completed by the treating physicians and bedside nurses and returned for analysis. This will be an additional way to assess the effectiveness of training, hypothesizing that if training provides sufficient resource-adapted information, prolonged interruptions related to infusion issues will be minimized by standardization.

Comparisons between pre- and post-training knowledge assessment surveys will be made to assess the adequacy of training materials in providing adequate and retained knowledge of drug administration. Comparisons will also be made with assessments done over time (at 3, 6, and 12 months post-training). McNemar’s test will be used to assess the change from pre- vs post-training.

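### The Aim 1 association tests make no allowance for staff sharing a site or answering repeatedly, so p-values for determinants that are shared within a site are too small

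*Protocol article*

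**What the plan says.** The statistical paragraph under Aim 1 of the Protocol article sets out the survey analysis: "The survey will be summarized by frequency tables and cross-tabulation to study any associations". It continues: "The chi-squared and Fisher’s exact test will be used to assess the associations". For the determinants it adds "Univariate and multivariable logistic regression analysis will be used, as appropriate, to study the correlations among scores of clinical infrastructure", readiness, climate and complexity "with implementation outcomes (feasibility, acceptability, and appropriateness) within and across institutions". A separate sentence covers change in barriers over the four time points and names no test for it.

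For knowledge, the section on training program evaluation says that McNemar's "test will be used to assess the change from pre- vs post-training".

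The data have this structure:

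- **Sites:** three pilot centres (Phase 1).
- **Respondents:** the implementation team at each site has at least two physicians, two nurses and one pharmacist (Study recruitment and informed consent). Knowledge surveys go to all trained staff.
- **Infrastructure:** one physician per pilot site completed the hospital questionnaire (Phase 2), so each site has one value.
- **Training:** "sessions conducted independently for each pilot site as two 90-min live, interactive virtual sessions" (Phase 3).
- **Waves:** Table 4 schedules "Pre-training, 3 and 6 months, and 1-year post-training". The Aim 1 text places the pilot sites' implementation assessments 1 year after training. The pilot knowledge survey is post-training only.

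The article names no random site effect, generalised estimating equation, cluster-robust error or stratification by site.

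**The concern.** Chi-squared, Fisher's exact and standard logistic regression all need independent rows. Five colleagues rating the readiness and climate of one hospital are not five independent observations of how readiness relates to feasibility. For infrastructure the position is starker: 15 respondents carry three distinct values of the predictor.

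If the rows are treated as independent, a peculiarity of one site is counted at least five times and can look like a determinant. The article asks which contextual factors correlate with successful implementation, and version 1.0 of the Implementation Roadmap is to be built from these three sites and then used for scale-out. A false determinant would therefore be carried to new centres.

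**Working it through.** The article states no alpha, power, sample size or ICC for these analyses, so there is no figure of the plan to reproduce. The 5% level and every ICC below are assumptions.

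**Inputs from the article.** 3 sites; at least 2 + 2 + 1 = 5 team members per site, so 3 × 5 = 15 respondents; 25 + 36 + 17 = 78 trained staff, a mean of 78/3 = 26 per site.

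**1. Site-level determinant, one wave.** With m people per site, the design effect is DE = 1 + (m − 1) × ICC. The true error of a nominal two-sided 5% test is 2 × [1 − Φ(1.96/√DE)].

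| Site ICC (assumed) | DE, m = 5 | Effective N of 15 | True error |
|---|---|---|---|
| 0.01 | 1.04 | 14.4 | 5.5% |
| 0.05 | 1.20 | 12.5 | 7.4% |
| 0.10 | 1.40 | 10.7 | 9.8% |
| 0.20 | 1.80 | 8.3 | 14.4% |

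This is a large-sample formula, so it was checked by simulation at the actual size. The layout was 3 sites × 5 staff, a yes/no answer from a latent normal scale with 50% yes, a predictor splitting one site from the other two, and no true association. The ICC is on the latent scale.

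| Test | No clustering | ICC 0.1 | ICC 0.3 |
|---|---|---|---|
| Chi-squared (uncorrected) | 4–5% | 8% | 16% |
| Fisher's exact | about 2.5% | 5% | 11% |

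Fisher's exact starts well below 5% because it is conservative with 15 rows. Clustering uses up that margin at ICC 0.1 and exceeds it at 0.3.

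**2. How much three sites can show.** A one-against-two split of three sites has only 3 possible arrangements, so a permutation test at site level cannot give p below 1/3. A small p-value for a site-level predictor can come only from treating colleagues as independent.

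**3. If waves were pooled.** With 5 people × 4 waves = 20 rows per site and within-person correlation r, DE = 1 + 3r + 16 × ICC. For ICC 0.05 and r = 0.3, DE = 1 + 0.9 + 0.8 = 2.7 and the error is 23%. For ICC 0.20 and r = 0.7, DE = 1 + 2.1 + 3.2 = 6.3 and the error is 44%. The article does not say that waves are pooled, and the pilot sites cannot supply the four scheduled waves. These figures only show what pooling would do at sites of this size that do.

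**4. McNemar's test.** Simulated with 26 staff at each of three sites: about 4% error when sites differ only in level, because pairing removes the level, and 18–28% when a site-by-time share of 0.05–0.10 is added. With 5 per site it stays conservative (0.6–2.7%). The 26 is the mean for the pilot sites, which have no pre-training survey, and stands in for future sites whose size is not given.

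**5. Opposite direction.** If change over time were tested as unpaired, the error would be 2 × [1 − Φ(1.96/√(1 − r))]: 2.8% at r = 0.2 and 0.03% at r = 0.7. Those p-values would be too large.

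**The case against.** The strongest reply is that this is a formative study that opens its analysis with descriptive statistics and states no alpha. The Roadmap also draws on interviews, clinical data and focus-group review, so a p-value alone does not create a determinant. Logistic regression is to be used as appropriate, within as well as across institutions. A within-site analysis removes site differences, and a mixed or generalised-estimating-equation logistic model is still logistic regression. Such choices are commonly left to an analysis plan, which is not shown here. And if Fisher's exact is used for 15 rows, the error at ICC 0.1 is about the nominal 5%.

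Much of this stands and limits the point. It does not remove it. The qualifier applies to the regression only; the chi-squared and Fisher's exact tests are named without it. The analysis is also meant to run across institutions, where the site effect does enter.

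A reader might go further, in three ways that the article does not support:

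- **That every named test treats every answer as independent.** McNemar's test pairs a person's own answers. It omits only site clustering of change and any wave beyond two.
- **That all p-values are too small.** An unpaired test of change would err the other way, and McNemar's test is too liberal only if sites differ in amount of change. Site-by-site training makes that plausible; nothing establishes it.
- **That pilot respondents each contribute four answers, or that McNemar's test is run on the 78 pilot trainees.** The pilot assessments come after training, so neither follows.

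**Conclusion.** The point holds for the Aim 1 association tests and for determinants that are constant or correlated within a site: infrastructure plainly, and readiness and climate to the extent that colleagues agree. At one wave with 3 sites of 5 staff, true type I error is about 8–16% for chi-squared and 5–11% for Fisher's exact at an assumed site ICC of 0.1–0.3, and it rises if waves are pooled. The size depends on ICCs that the article does not give; the direction for site-level predictors does not. For knowledge change the point is conditional: it concerns only future sites with a pre-training survey, and only if they differ in amount of change. This should be corrected before the surveys are analysed. It does not undermine the descriptive or qualitative parts of the study.

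**What to change.** In the Aim 1 statistical paragraph:

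- Name the site as the cluster and the person as the repeated unit, and report survey results by site.
- Give site-level predictors, such as infrastructure, descriptively with no p-value while there are only three sites.
- Test person-level associations within site, for example by a permutation test stratified by site that permutes whole persons with all their waves together.

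In the training evaluation section, report knowledge change per site. Combine it across sites, with a small-sample cluster method, only once enough future sites have both pre- and post-training data.

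Two tempting shortcuts are weak with three sites. A mixed model would have about 2 degrees of freedom for site. A rule that the direction must agree at all three sites is met by chance 2 × (1/2)³ = 25% of the time.

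The cost is analysis wording only, with no new data. The downside is wider intervals and fewer nominally significant results.
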